##### Quality of the carer-patient relationship scale

The 14-item measure invites the respondent to state their level of agreement with questions about their relationship with the person for whom they care [32]. It will be completed by carers. The responses are scored from 1 to 5, and the total score is out of 70, with a higher score indicating higher perceived relationship quality.

##### Carers of older people in Europe scale

The 15-item scale asks the carer about their experiences of caregiving and its consequences for their physical and mental health [33]. The responses are scored from 1 (never) to 4 (always). The 15 questions are presented together, but when total scores are calculated they are divided into three subscales which are treated separately in analysis: negative impact of caregiving, positive value of caregiving and quality of support. The precedent for the use of these subscales in analysis is set in one of the paper describing the original development of COPE [34].

##### Short sense of competence questionnaire

The SSCQ is derived from the Zarit Burden Inventory and evaluates the carer’s experience of caring across seven items [35]. The carer indicates how strongly they agree with the statements in the scale and each item is scored from 1 to 5. A higher score indicates a higher perceived sense of competence.

##### Client service receipt inventory

The CSRI is a tool to measure consumption of services with a view to estimating their costs for economic analysis [36]. It will be administered in a form adapted to the typical activities of people with dementia and their carers, in order to measure the use of health and social carer resources by each participant. This instrument will be completed by the carer.

#### Qualitative data

Previous research into group singing for people with dementia has shown that quantitative measures may not capture the benefits perceived by participants [14, 37]. Qualitative data concerning participants’ experience of the singing groups will be collected during the study using participant observation. BD will conduct structured in-person observations of 3-4 opportunistically selected dyads in each singing group, including both intervention and control group participants. Each dyad will be the focus of observations three times: in one early session, in one session towards the middle of the group’s course, and in one later session. Detailed notes on the observations will be made after the sessions.

We will also collect qualitative data from a sub-sample of participants through semi-structured interviews. We will aim to interview 10 dyads in total, 12.5% of the 80-dyad intended sample. Dyads will be selected for interview opportunistically and those who do not wish to be interviewed will be free to decline. We will interview at least one dyad from each singing group and will aim to spread the sample evenly between the groups. Interviews will last 30-45 min, and each dyad will be interviewed together where possible. The interview guide will focus on understanding participants’ experience of taking part in the group. Interviews will be audio recorded if possible; if participants decline to be recorded, we will seek their permission to make written notes during the interviews.

### Data management

Each participant will be assigned a trial identity code number, for use on case report forms (CRFs) and in the database. The trial documents and database will also use participants’ initials, sex and date of birth. Data will be recorded for each participant using paper CRFs. The data from these forms will be entered into the trial database and stored electronically. Access to the database will be password protected and restricted to trial personnel, who will each have a unique login code and PIN. The paper CRFs will be stored in a locked cupboard on the University of Nottingham premises. Consent forms (which contain participants’ real names) will be stored separately in a different locked cupboard. Participant’s names and contact information will be securely stored on a separate part of the database system, not associated with their trial data.

Any video or audio recordings taken during data collection will be transferred daily from the recording device to password-protected encrypted drives on University of Nottingham computers. They will then be deleted from the recording device.

Data will be stored securely for 7 years after the last person has been recruited. All data will be analysed on University of Nottingham computers and backed up to the University of Nottingham servers. Only members of the research team authorised by the data custodian will have access to the research data.

### Data coding and analysis

#### Statistical analysis of quantitative data

Quantitative data analysis will be conducted by the study statistician (BG), using the software package Stata 16. The data analysis will be mainly descriptive [38]. All measures will be summarised with mean and standard deviation (S.D.) for normally distributed variables, median and inter-quartile range (IQR) for skewed variables, and frequency (%) for response of categorical variables, by intervention arm across follow-up time. Analysis of Co-variance (ANCOVA) will be performed to quantify treatment effect size and its precision by means of regression modelling with baseline measures as covariate, and to derive the change from baseline score for each arm. Due to the non-independence of patient-carer dyad measures and with data being measured repeatedly, multivariate, multilevel modelling will be performed to account for the association between the same kind of outcome measure of patient-carer data and repeated data. We will calculate recruitment rate, retention rate and attrition rate, exploring patterns of missing data and drop out from the intervention group and the waiting list control group. All results will be used to inform future definitive trial design.

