### Intervention

The intervention in this study is attendance at weekly singing group sessions for 10 weeks. Each session will include approximately 60 min of warm-up activities and singing, with about 30 min for refreshments and socialising before or after the session. The sessions will be run jointly by two professional community musicians who have extensive experience of running similar singing groups together. The format of the sessions includes a full physical and vocal warm-up, followed by singing familiar songs accompanied by guitar. Themed songbooks will be provided for participants; each week a different songbook will be selected by the facilitators, so each session will have a different theme. Themes might include songs about the weather, from a particular era, or relating to the current season (e.g. Christmas, summer). Singing group participants will be encouraged to choose their favourite songs from the books for the whole group to sing. The facilitators’ approach will emphasise that the aim of the group is to sing for fun and enjoyment, and that the participants’ musical skills or singing voices are not being assessed or judged.

The content of each session will be fully documented, and three out of every ten sessions will be video recorded in order to check that the intervention is delivered consistently. Attendance at singing sessions will be monitored and recorded. Participants will be free to miss individual sessions or withdraw from the singing group entirely as they wish, and they do not need to give a reason.

Since each singing group can accommodate up to 20 dyads, we propose to run four groups in total in two different geographical areas. The first two groups will be set up for those allocated to the intervention group; after the 3 month waiting period, we will start another two groups for those in the waiting-list control group. There is provision for those in the intervention group to continue to attend the singing groups after the initial 10-week period, if they wish to. This is for ethical reasons and to facilitate embedding the groups into the local community, as discussed later in the “Ethics and dissemination” section. Continued attendance by participants in the intervention group will not compromise the primary objectives of recruitment, retention and acceptability, and its effects on the 6-month data collection are considered an acceptable trade-off.

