### Control condition

Participants who are allocated to the waiting-list control group will receive care as usual during the 3 months that they will be required to wait before beginning to attend a singing group. They will be requested to abstain from attending other organised group singing activities during this time, with the exception of religious services.

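### The planned models allow for dyads and repeated visits but not for the singing group, so if outcomes correlate within groups the intervals around the effect sizes will be too narrow

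*Protocol article*

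**What the plan says.** In the protocol article, the section on statistical analysis of quantitative data states that "Analysis of Co-variance (ANCOVA) will be performed to quantify treatment effect size and its precision", with the baseline score as covariate. It then gives its reason for a further model, "Due to the non-independence of patient-carer dyad measures and with data being measured repeatedly", and says that "multivariate, multilevel modelling will be performed to account for the association between the same kind of outcome measure of patient-carer data and repeated data". Neither singing group nor area is named as a level or covariate. The section ends by saying that the results will feed the design of the definitive trial.

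The section on allocation and blinding makes the dyad the unit of randomisation and stratifies by sex and Clinical Dementia Rating only.

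The Intervention section describes how treatment is delivered: "Since each singing group can accommodate up to 20 dyads, we propose to run four groups in total in two different geographical areas". It adds that "The first two groups will be set up for those allocated to the intervention group" and that, after the waiting period, "we will start another two groups for those in the waiting-list control group". Under Control condition, waiting-list dyads "will receive care as usual during the 3 months that they will be required to wait before beginning to attend a singing group".

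**The concern.** Dyads are randomised one by one but treated together. Members of a group share a venue, a set of sessions, the songs chosen and the time for socialising. The Introduction presents bonding and mutual support among attenders as part of how singing may work. The intervention can therefore make the outcomes of dyads in the same group alike, a dependency that neither the dyad nor the repeated-measures structure captures.

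The structure differs by visit. At 3 months the design is partially nested: intervention dyads sit in two groups, while waiting-list dyads have not yet been grouped. At 6 months both arms have been in groups.

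At stake is the precision the analysis sets out to report. A model that ignores positive within-group correlation understates the standard error of the effect, and those estimates are meant to inform a larger trial of the same group intervention.

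**Working it through.** **The plan's own figure.** The only sample size tied to an effect size is the 360 dyads for an effect of 0.3 under Study objectives. The article gives neither alpha nor power; assume two-sided 5% and 80%. Then n per arm = 2 × (1.960 + 0.842)² / 0.3² ≈ 174.4, rounded up to 175, or 350 dyads. The stated 360 is within 3% of this (power about 81% at 180 per arm). At 90% power the total would be 468. So 360 is close to a calculation for independent dyads, under assumed inputs.

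**Inputs for the check.**
- Group size m: up to 20 (Intervention), with 40 dyads per arm (Sample size).
- Smaller m: 70% retention (Endpoints) gives 0.7 × 20 = 14. If the 70% recruitment criterion is read as 70% of 80, an assumption, then 56 × 0.7 / 4 = 9.8, about 10.
- ICC: not in the document. Assumed 0.01, 0.05 and 0.10, after baseline adjustment.
- Equal arm sizes and equal total variance in the two arms.

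**Formulas.** Design effect of a grouped arm: DE = 1 + (m − 1) × ICC. True SE divided by reported SE:
- 3 months, intervention arm grouped only: √((DE + 1) / 2)
- 6 months, both arms grouped: √DE

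Example with m = 20 and ICC = 0.05: DE = 1 + 19 × 0.05 = 1.95. The 3-month ratio is √(2.95 / 2) = 1.21 and the 6-month ratio is √1.95 = 1.40.

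| m | ICC | DE | SE ratio, 3 months | SE ratio, 6 months |
|---|---|---|---|---|
| 20 | 0.01 | 1.19 | 1.05 | 1.09 |
| 20 | 0.05 | 1.95 | 1.21 | 1.40 |
| 20 | 0.10 | 2.90 | 1.40 | 1.70 |
| 14 | 0.01 | 1.13 | 1.03 | 1.06 |
| 14 | 0.05 | 1.65 | 1.15 | 1.28 |
| 14 | 0.10 | 2.30 | 1.28 | 1.52 |
| 10 | 0.01 | 1.09 | 1.02 | 1.04 |
| 10 | 0.05 | 1.45 | 1.11 | 1.20 |
| 10 | 0.10 | 1.90 | 1.20 | 1.38 |

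**What this does to an interval.** With 40 dyads per arm and no baseline adjustment, the reported 95% half-width is 1.96 × √(2/40) = 0.438 SD. At 3 months with m = 20 it should be 0.459, 0.532 or 0.612 SD for the three ICCs. Actual coverage of the reported interval is 2Φ(1.96 / ratio) − 1, which gives about 94%, 89% and 84%. A simulation of two groups of 20 against 40 ungrouped controls (20,000 runs) gave 93.7%, 89.6% and 83.9%. With m = 10, coverage is about 94%, 92% and 90%. At 6 months with m = 20 it is about 93%, 84% and 75%.

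**The case against.** Several arguments limit the point, and most of them stand.

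- **The consequence is conditional.** The document gives no ICC. At 0.01 the understatement is 5% or less at 3 months, which is small. The two musicians lead sessions jointly to a common format, with content documented and some sessions filmed to check consistency. This removes one usual source of difference between groups. Venue, group composition and peer influence remain.
- **Twenty is a ceiling.** Recruitment was slow (Discussion), so the smaller values of m in the table may be nearer the mark.
- **The analysis is largely descriptive.** A reader might infer an inflated false-positive rate, but the article specifies no hypothesis test or efficacy threshold for these outcomes, so no planned decision would be wrong at that rate. Nor is the go/no-go assessment compromised: recruitment, retention and acceptability of the control do not rest on these models.
- **The 360 is not shown to be wrong.** It is tempting to conclude that a design effect was left out of the full-trial size. Alpha, power and any allowances are unstated, and the definitive protocol is still to be written, so the match with 350 is suggestive only.
- **Two groups per arm cannot yield a usable ICC.** Adding the level to the model would not by itself cure the interval or give the planning value.
- **This is a condensed article.** A fuller analysis plan might add the level. But the article does not merely leave the model open: it names the dependencies the model is there to handle, and the delivery group is not one of them. This last argument does not remove the point.

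**Conclusion.** The point holds in conditional form. Followed as written, the plan gives intervals that ignore a dependency the intervention itself can create. If the within-group ICC lies between 0.01 and 0.10, the true 3-month standard error is 5% to 40% larger than reported with 20 dyads per group, and 2% to 20% larger with 10. At 6 months with 20 per group it is 9% to 70% larger. If the ICC is zero, nothing is lost. These figures rest on assumed ICCs, equal arms and equal group sizes. The effect is confined to the secondary effect estimates and their use in designing the definitive trial. The document does not support saying that the intervals are certainly too narrow, or that the feasibility conclusions are at risk.

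**What to change.** In the statistical analysis section:

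1. Name singing group as a source of clustering, in the intervention arm only at 3 months and in both arms at 6 months.
2. Report each effect with its model-based interval, and again with the variance of each grouped arm multiplied by 1 + (m − 1) × ICC, using the achieved group sizes and ICCs of 0.01, 0.05 and 0.10.
3. State that the unadjusted interval is conditional on these particular groups.
4. State that two groups per arm cannot give a reliable ICC, so the definitive trial must take one from elsewhere.

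Area may be added as a covariate. It takes up differences common to both arms within an area but does not remove effects specific to one group, so it does not replace step 2.

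The cost is a few sentences, one small table and somewhat wider intervals. Recruitment, randomisation and data collection do not change.

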#### Analysis of qualitative data

Recordings/notes from interviews and observational notes will be transcribed as necessary and analysed using NVivo 12. The technique for analysis will be the ‘general inductive approach’ in which the coding is largely guided by evaluation objectives [39]. The evaluation objectives in this case will be the feasibility of the study design and the experiences of all participants who attend a singing group.

BD will undertake the first stage of the analysis and will assign first-order codes to the data. Through discussion with the rest of the research team, second-order codes will then be developed. In order to enhance the validity of the coding process, a sample of transcripts and notes will be coded by another member of the research team, and any disagreements between coders will be discussed.

### Data monitoring

A trial Data Management and Ethics Committee (DMEC) will be formed, consisting of members who are not part of the University of Nottingham. All the members of the DMEC will have experience of running clinical trials, and the group will include a statistician, an academic and a clinician. The Chief Investigators (JS & MO) will be the data custodians.

### Adverse events

The occurrence of an adverse event as a result of participation in this study is not expected due to the nature of the intervention, which is a non-clinical intervention based on social music-making and has no known side effects. However, in order to provide further assurance of the safety of the intervention, data on Severe Adverse Events (SAEs) will be collected for people with dementia and their carers during follow-up data collection at 3 and 6 months. Additionally, attendance at the group will be monitored by the singing group facilitators and the research associate, so any SAE which occurs amongst the group members will be recorded. These include hospitalisation, extension of hospitalisation, other serious medical events and death. Such SAEs might conceivably be related to participation in the intervention if they were associated with falls, emotional arousal or depression.

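### For the first 3 months only the singing arm has a second route for detecting SAEs, so any between-arm SAE tally would lean against singing unless it is limited to the contacts both arms share

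*Protocol article*

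**What the plan says.** The Adverse events section of the protocol article sets out two routes for detecting SAEs.

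- **Scheduled follow-up, all participants.** SAE data "will be collected for people with dementia and their carers during follow-up data collection at 3 and 6 months".
- **Session monitoring, group members.** Facilitators and the research associate also keep track of who attends the groups, and the section draws from this the consequence "so any SAE which occurs amongst the group members will be recorded".

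The section gives the purpose as added reassurance that the intervention is safe. It names falls, depression and strong emotion as ways in which an event might be linked to taking part.

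Two other sections fix who has the second route and when. Under Intervention, the singing arm has "attendance at weekly singing group sessions for 10 weeks". Under Control condition, waiting-list participants "will receive care as usual during the 3 months that they will be required to wait before beginning to attend a singing group". The Intervention section confirms that their groups come later: "after the 3 month waiting period, we will start another two groups for those in the waiting-list control group".

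Under Allocation and blinding, follow-up data are collected by researchers blinded to allocation, while those delivering the sessions know it.

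**The concern.** From baseline to 3 months, the only period in which one arm sings and the other does not, the two arms are not watched in the same way. Singing dyads can have an SAE noted at any of ten weekly sessions and again at the 3-month visit. Waiting-list dyads have the visit alone, and the article describes no equivalent interim contact for them. The extra route is also run by people who know the allocation, whereas the shared route is blinded.

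Hospital admission and death can occur in this population without singing, so a reader of the results will naturally set the singing arm's count beside the waiting arm's. If visits miss some events, that comparison shows an excess in the singing arm even when the true risks are equal. A later analysis plan can separate the routes only if the source of each event was recorded when it was collected.

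**Working it through.** **No figure to reproduce.** The article states no SAE risk, capture rate or safety power. What follows illustrates direction and plausible size.

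**Inputs from the article**
- 40 dyads per arm (Sample size).
- Visits at 3 and 6 months for all; weekly sessions for 10 weeks in the singing arm; no sessions in the waiting arm for 3 months (Adverse events, Intervention, Control condition).

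**Assumptions, not in the article**
- p, the true chance of an SAE per dyad over 3 months, equal in both arms: 5% to 20%.
- v, the chance that an SAE is captured at scheduled follow-up, equal in both arms: 0.6 to 1.0. It covers both attending the visit and reporting the event.
- s, the chance that an SAE is captured through sessions, independent of v: 0.3 to 0.8.

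**Formulas**
- Expected recorded events, waiting arm: 40 × p × v.
- Expected recorded events, singing arm: 40 × p × [1 − (1 − v)(1 − s)].
- Ratio, singing to waiting: [1 − (1 − v)(1 − s)] / v = 1 + s(1 − v)/v.
- Difference in events: 40 × p × s × (1 − v).

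The ratio does not depend on p. It cannot fall below 1, because a second route can only add recorded events.

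**Results for the ratio**

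| v | s = 0.3 | s = 0.8 |
|---|---|---|
| 1.0 | 1.00 | 1.00 |
| 0.9 | 0.93/0.90 = 1.03 | 0.98/0.90 = 1.09 |
| 0.8 | 0.86/0.80 = 1.075 (shown as 1.07) | 0.96/0.80 = 1.20 |
| 0.6 | 0.72/0.60 = 1.20 | 0.92/0.60 = 1.53 |

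**Results in events**
- Middle example (p = 10%, v = 0.6, s = 0.5): singing 40 × 0.10 × 0.80 = 3.2; waiting 40 × 0.10 × 0.60 = 2.4; the true number is 4 in each arm. The artificial excess is 0.8 of an event.
- Largest case in the range (p = 20%, v = 0.6, s = 0.8): 7.36 against 4.80, an excess of 2.56.
- Smallest case with imperfect visits (p = 5%, v = 0.9, s = 0.3): 1.86 against 1.80, an excess of 0.06.

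**After the fix.** If both arms are counted through the scheduled contacts only, each arm's expected count is 40 × p × v and the ratio is 1.00 for every v and s.

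**The case against.** The strongest reply is that the article never plans the comparison that would be biased. The statistical analysis section summarises measures "by intervention arm across follow-up time", and a reader might infer that SAEs are included. But that section deals with the outcome instruments, and SAEs appear neither there, nor in the table of outcome measures, nor among the endpoints. The safety text is framed around whether an event could be related to participation, and for that purpose closer watching of exposed people is useful. This stands, so the point is conditional on a between-arm tally being made.

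Three further readings are tempting and are not supported.

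- **That a control SAE rate that is too low feeds the full trial.** The Study objectives and Endpoints sections carry forward recruitment, retention, acceptability and the choice of outcome measures, and the full trial is sized on quality of life. No SAE rate is carried forward.
- **That waiting-list dyads who miss the 3-month visit contribute nothing.** The article does not say so. The team must contact these dyads at about that time to invite them to a group, and the proportion who start is its most important criterion. The 6-month visit may recover some events. At attended visits in either arm, the service-use inventory gives a further prompt about health care.
- **That the distortion could reach about 1.7.** That follows from fixing capture in the singing arm at 95% while applying 30% visit loss and 80% recall to controls alone: 0.95 / (0.70 × 0.80) = 1.70. With the same visit capture of 0.56 in both arms, 95% overall would need session capture of (0.95 − 0.56)/0.44 = 0.89. That is hard to credit when participants may miss sessions or leave without giving a reason. The 70% retention figure is also a threshold for proceeding, not an expected loss among controls.

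Finally, SAE form details are commonly left to the full protocol, and their absence from an article is no fault. The point here rests on what the article does state: an extra detection route tied to attendance, and therefore to allocation, during the randomised period.

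**Conclusion.** The unequal detection is built into the stated design for months 0 to 3. Its direction is known: with equal true risk and equal visit capture in the two arms, the expected recorded ratio is at or above 1, against singing. It is exactly 1 only if scheduled follow-up finds every event. Its size cannot be derived from the article. On the assumed session capture of 30% to 80%, it is small if visits capture 90% of events (1.03 to 1.09), modest at 80% (1.07 to 1.20) and material at 60% (1.20 to 1.53). In counts it ranges from a fraction of an event to between two and three.

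The calculation also assumes that the two routes work independently and that dyads are lost from visits equally in both arms. After 3 months the waiting arm attends groups too, so the argument is confined to the randomised period.

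Importance is minor to moderate. Safety is not a feasibility criterion and the analysis is mainly descriptive, but the article gives a safety purpose for these data and the remedy is cheap.

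**What to change.** 1. Add a field to the SAE form for how the event came to light: session, scheduled follow-up contact, or both. At the 3- and 6-month contacts, ask the SAE question in the same way in both arms, whether or not a session had already noted an event.
2. State that any between-arm tally counts only events found at the 3- and 6-month contacts, and list session-detected events separately so that no safety information is lost.
3. When a visit is missed and consent still stands, put the same SAE question by telephone, in both arms.

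The cost is one form field, a few calls and fewer events in any by-arm table. The field has to be in place before data collection. The Discussion section reports that recruitment was paused, and baseline data are to be collected only when groups are about to start, so it could be added in time.
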